### Safety evaluation

In this study, the categories and severity of adverse events (AEs) should be recorded on the CRF in detail after each intervention, such as falls, joint injuries, hypertension, headache, dizziness, lumbago, tinnitus, chest oppression, etc. Incidence of AEs will be reported as the number of AEs by number of Tai Chi sessions. If AEs do not improve after adequate rest, prompt medical treatment should be applied to the participants. In the event of a severe adverse event (SAE), the principal investigator and ethics committee should be fully informed within 24 h of the occurrence, who are expected to provide guidance for further evaluation and management and make decisions on whether to suspend the trial. Investigators should also pay sustained attention to participants who experience any AE until it is resolved, especially those who have withdrawn due to AEs. In addition, participants will receive appropriate medical and financial compensation if AEs have been shown to be associated with the interventions in this study.

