## Abstract

**Background:**

Knee osteoarthritis (KOA) is a common public health problem and a leading cause of long-term pain, decreased muscle strength, and even disability. Tai Chi has been proved effective and highly recommended for KOA management worldwide. However, little is known about its benefits on quadriceps strength which is closely associated with relieving knee pain. This trial is designed to evaluate the efficacy and safety of Tai Chi on knee pain and muscle strength in middle-aged and older adults with KOA.

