**Methods:**

A total of 100 participants will be randomly divided into a Tai Chi group (TC group) (1x/week for 12 weeks) and a control group with a health education and stretching program (1x/week for 12 weeks) with a follow-up period of 6 weeks. The primary outcome is the change of Western Ontario and McMaster Universities (WOMAC) pain subscale at week 12 compared with baseline. Secondary outcomes include WOMAC stiffness and function subscales, data from isokinetic dynamometry, gait analysis with electromyography (EMG), and a 36-item short form health survey (SF-36). The daily dose of pain-relieving medication will also be recorded. All adverse effects will be assessed by the Treatment Emergent Symptom Scale (TESS).

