### Randomization and allocation concealment

Recruited participants will begin intervention within 1 week of baseline assessment. An independent statistician will use SPSS (version 26.0) to generate the random sequence with a random block size of 2–6. Eligible participants will be randomly assigned to either the TC group or the control group on a 1:1 ratio. Random numbers and assigned groups will be sealed in opaque envelopes, which will be numbered sequentially. The envelopes will not be delivered and opened by a study coordinator until written consent forms and baseline assessments have been completed. The study coordinator will then inform eligible participants of their group allocation and schedule of training sessions by telephone. This trial will be conducted in five cycles of at least 18 participants per cycle for a 12-week intervention course, to ensure a consistent environment for interventions and to maintain an equal number of participants in each group.

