### Interventions

#### Tai Chi group

Based on the guidance of Tai Chi masters and previous high-quality KOA studies [25, 29], this simplified Yang-style Tai Chi protocol will be adopted for KOA participants to avoid sustained weight bearing, dynamic rotation of knee joints, and excessive knee flexion. Eight-form Tai Chi is expected to be easily comprehensible for older participants and more suitable for physical conditions of knee osteoarthritis without excessive stress on the joints. Participants in TC group will receive a 60-minute weekly training session for 12 weeks. Each session consists of 10 min of warm-up, 40 min of Tai Chi practice and 10 min of cool-down activities. The training protocol includes eight Tai Chi forms: starting posture, forearm rollings on both sides, brush knee and twist steps on both sides, part the wild horse’s mane on both sides, wave hands like clouds, golden rooster stand on one leg, kick with heel, grasp the bird’s tail on both sides, cross hands and closing form. All movements of 8-form Tai Chi are shown in Fig. 2. The protocol will follow an easy-to-tough pattern, with the first phase (week 0–1) focusing on communicating effectively with participants and practicing Tai Chi preparatory movements, the second phase (week 2–4) focusing on learning and practicing eight Tai Chi forms, and the third phase (week 5–12) focusing on practicing and strengthening the sequence and precision of the forms under the guidance of the instructor.

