**Fig. 2 Fig2:**
[figure not shown]
All movements of 8-form Tai Chi

Participants will also be instructed to practice Tai Chi for 30 min daily at home. Pre-recorded Tai Chi training videos on a WeChat mini-app are made to prevent participants from forgetting details while practicing at home. All participants will be encouraged to maintain their usual physical activities and to perform no additional strength training other than Tai Chi exercises.

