#### Attention control group

Participants in the control group will receive a 60-minute weekly health education and stretching program for 12 weeks. It has been successfully applied in other studies as passive control [22, 29], aimed at controlling attention from individuals, motivating enthusiasm for recruitment, attendance, and adherence without affecting main outcomes during the trial. Each session starts with 40 min of lectures on KOA knowledge, including diagnostic criteria, diet and nutrition, pain management, wellness and lifestyle changes, physical and mental health education, and medical management. Orthopedic surgeons, physiatrists, and health consultants from hospitals will deliver these educational lectures for participants. The final 20 min of the hourly session consists of stretching exercises involving the upper body, trunk and lower body. Participants will also be instructed to practice stretching exercises for 30 min daily at home. All participants will be encouraged to maintain their usual physical activities and to perform no additional strength training other than stretching exercises.

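### The only adverse-event rate the protocol defines has no denominator in the control arm, so that measure cannot support a between-group safety comparison

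*Protocol article*

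**What the plan says.** The Background of the abstract gives the purpose: "This trial is designed to evaluate the efficacy and safety of Tai Chi on knee pain and muscle strength". The Safety evaluation section asks for the type and severity of events to be entered on the case report form after each intervention. It then fixes how incidence is expressed: "Incidence of AEs will be reported as the number of AEs by number of Tai Chi sessions". The article defines no other AE rate, and the section on data collection and statistical analysis adds no safety measure and no comparison of AEs between arms.

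The trial has two arms of equal planned size: "Eligible participants will be randomly assigned to either the TC group or the control group on a 1:1 ratio". For the Tai Chi arm, "Participants in TC group will receive a 60-minute weekly training session for 12 weeks", and on top of this, "Participants will also be instructed to practice Tai Chi for 30 min daily at home". For the other arm, "Participants in the control group will receive a 60-minute weekly health education and stretching program for 12 weeks"; home stretching of the same daily length is also prescribed. Table 1 marks AEs at weeks 0, 6, 12 and 18 with no distinction by arm, while the intervention ends at week 12.

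**The concern.** A rate whose denominator exists in only one arm cannot be compared between arms. Several of the events listed in the Safety evaluation section, such as headache, dizziness, hypertension and lumbago, can be expected to occur in adults aged 40 or older whatever exercise they do. The control arm shows that background. If the stated rule is followed literally, the control arm contributes nothing to the reported incidence, and the reader gets one descriptive figure for Tai Chi with nothing to set it against.

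A second, smaller problem lies inside the Tai Chi arm. The article uses the word session for the weekly class and describes home practice separately. A count of events over 18 weeks, some of them possibly during home practice or follow-up, would then be divided by a count of classes alone.

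**Working it through.** The article attaches no figure to AE incidence, so there is none to reproduce. The check is of the denominators.

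**Inputs.** 100 participants at 1:1, hence 50 per arm (Sample size calculation; Randomization). 12 weekly classes of 60 minutes, of which 40 minutes are Tai Chi practice (Tai Chi group). 30 minutes of home Tai Chi daily (text following Fig. 2). No duration is given for home practice; 12 weeks, or 84 days, is assumed here, and 60 to 126 days is tested. AE visits at weeks 0, 6, 12 and 18 (Table 1).

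**Step 1: denominator by arm, as planned.**
- Tai Chi: 50 × 12 = 600 participant-sessions.
- Control: 50 × 0 = 0 Tai Chi sessions. The rate is AEs / 0, which is undefined.

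**Step 2: share of prescribed Tai Chi time that falls in class.** Home share = home minutes / (home minutes + class minutes).
- Home: 84 × 30 = 2,520 minutes.
- Class, whole hour counted: 12 × 60 = 720 minutes. Total 3,240. Class share 720 / 3,240 = 22%; home share 78%.
- Class, Tai Chi part only: 12 × 40 = 480 minutes. Total 3,000. Class share 480 / 3,000 = 16%; home share 84%.

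**Step 3: sensitivity to the assumed duration and adherence.**
- 60 home days, whole hour counted: 1,800 / (1,800 + 720) = 71%.
- 126 home days, Tai Chi part only: 3,780 / (3,780 + 480) = 89%.
- At 84 days, home practice stays the larger part unless home adherence falls below 720 / 2,520 = 29% (whole hour) or 480 / 2,520 = 19% (Tai Chi part only).

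**Step 4: period.** The last class is at week 12 and the last AE visit at week 18. Events from those six weeks have no sessions to go with them.

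**Step 5: a denominator that both arms share.** At full follow-up each arm has 50 participants and 50 × 18 = 900 participant-weeks from week 0 to week 18, so both a proportion and a rate are defined in each arm.

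A side point: the denominator could be read as 600 participant-sessions or as 60 classes held (5 cycles × 12, assuming one Tai Chi class per cycle). The two readings differ tenfold.

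**The case against.** The strongest reply is that naming one incidence figure does not rule out AE tables by arm, which an article commonly leaves to the full protocol or analysis plan. AEs are scheduled without restriction by arm, and categorical variables are to be summarised as n (%), so affected participants could be counted in each arm from data already planned. This stands. A reader might infer that the safety question cannot be answered by comparison at all; the documents do not support that.

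Two other strong readings also fail. One is that the rule leaves out home-practice or follow-up events. The sentence sets a denominator and excludes no event from the numerator; Table 1 records AEs at week 18. The other is that the rate is made to look small by a large denominator. If home events are counted, class sessions are too few rather than too many. As an illustration only, 15 events over 600 sessions is 2.5 per 100, whereas over 50 × (12 + 84) = 4,800 practice occasions it is about 0.3 per 100. The direction of any distortion is not established.

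It is also fair to say that safety appears in the abstract's statement of purpose but not among the two numbered objectives in the Introduction, and that the sample size rests on WOMAC pain alone.

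None of this supplies a control-arm denominator. The article did not leave the measure open; it stated one that does not fit a two-arm design.

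**Conclusion.** The point holds for the stated measure. Followed as written, it yields a rate for the Tai Chi arm (600 planned participant-sessions) and none for the control arm (zero). This follows from the design and needs no assumption.

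The mismatch of exposure within the Tai Chi arm is a possibility, not a certainty. It depends on session meaning the weekly class, which is the article's own usage, and on which events enter the numerator. The figure of about 22% of prescribed time in class assumes 84 days of home practice at full adherence and counts the whole class hour; over 60 to 126 home days and both ways of counting class time, the home share runs from 71% to 89%. Nothing in the article says where events are more likely to happen.

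The primary efficacy analysis is not touched. This should be corrected, because it bears on a stated purpose and the correction is cheap.

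**What to change.** Replace the incidence sentence in Safety evaluation with: *For each arm, report the number and percentage of participants with at least one AE, and AEs per participant-week from week 0 to week 18, with the between-group difference and 95% CI.* The period starts at week 0 because Table 1 begins AE recording there, while randomisation is at week −1. AEs per attended class session may be kept as a supplement, given for both arms.

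Separately, confirm that AEs, including those during home exercise, are recorded in the same way and at the same times in both arms. The article ties recording to each intervention and does not mention home events explicitly. If they are already captured alike, the whole change is wording plus slightly more reporting work. If they are not, data collection has to change in a trial whose recruitment has begun, and that should be settled early.

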### Adherence

At the beginning of the study, a group of people interested in Tai Chi will be selected to volunteer for the trial. Participants have the right to choose whether or not to participate after a thorough understanding of the assigned groups and procedures. Participants will be encouraged and informed of the detailed exercise contents and benefits once a week via WeChat or telephone. Researchers will visit training sessions and regularly review course videos to monitor the veracity of interventions. Their attendance at each session will be recorded in attendance forms by study assistants who are not involved in intervention, evaluation and data analysis. We will track the reasons for missed sessions and the number of missed sessions. In addition, participants will be required to upload photos or videos of home exercises to provide feedback to instructors and will be encouraged to complete their daily punches on a WeChat mini-app. Pre-recorded Tai Chi training videos will be made to prevent participants in TC group from forgetting details while practicing Tai Chi at home.

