### Quality control

Quality control will be carried out under the supervision of the independent steering committee to eliminate potential bias and ensure the quality of the trial. Steering committee consists of investigators with expertise in Tai Chi clinical trials, statistical design, exercise, and adverse events. They are responsible for monitoring data, identifying problems, reviewing collected data, and controlling bias. To ensure consistency in delivery, the protocol will remain the same throughout the 12-week training period. All instructors and assessors must receive standard training prior to the commencement of the trial. The Tai Chi instructor with extensive experience will be required to receive standard training sessions by a nationally recognized academic specialist with more than 20 years of Tai Chi training prior to the initiation of this trial. Training sessions should be conducted in strict accordance with the Tai Chi protocol, including Tai Chi forms, Tai Chi principles, breathing techniques, concentration, and KOA precautions. Both groups will be conducted simultaneously in small groups with at least 9 participants per class to avoid varying severity of KOA depending on the seasons and weather. For participants, they must upload photos or videos of home exercises to provide feedback to instructors and are encouraged to complete their daily punches on a WeChat mini-app. No additional exercises will be assigned to them during the study period. To maintain consistency in individual Tai Chi intensity, all participants will be required to exercise at a moderate intensity of 50-70% of maximum heart rate (calculated as 220-age, beats/minute) for 60 min. In this study, both heart rate and activity intensity will be recorded using Actigraph wGT3X-BT (ActiGraph LLC, Pensacola, FL), which will be worn on the patient’s waists during Tai Chi at the 1st, 6th and 12th intervention. To ensure pre-specified exercise intensity, participants will be trained to wear Actigraph before exercise to measure intensity. If necessary, the Tai Chi instructor will adjust the number and range of movements to achieve the pre-specified intensity. As for pain-relieving medications, participants will be allowed to continue their routine medications to alleviate pain. Any changes in dosage should be recorded in CRFs, but changes to the medical regimen will not be recommended by researchers.

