## Abbreviations

AC: Attention Control
AEs: Adverse Events
ANOVA: Analysis of Variance
AP: Average Power
BP: Bodily Pain
CONSORT: Consolidated Standards of Reporting Trials
CRF: Case Report Form
EMG: Electromyography
GH: General Health
IQR: Interquartile Range
KOA: Knee Osteoarthritis
LOCF: Last Observation Carried Forward
MH: Mental Health
MVC: Maximal Voluntary Contraction
NSAIDS: Nonsteroidal Anti-inflammatory Drugs
PF: Physical Functioning
PPS: Per-Protocol Set
PT: Peak Torque
PTA: Peak Torque Angle
PW: Peak Work
RE: Role Limitations due to Emotional Problems
RP: Role Limitations due to Physical Problems
SAE: Severe Adverse Event
SF: Social Functioning
SF-36: 36-item Short Form Health Survey
SPIRIT: Standard Protocol Items:Recommendations for Interventional Trials
TC: Tai Chi
TESS: Treatment Emergent Symptom Scale
VT: Vitality
TW: Total Work
WOMAC: Western Ontario and McMaster Universities

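### Expedited safety reporting is triggered by severity and timed from the event, so a serious but non-severe event can escape it and the stated contact schedule does not assure the 24 h limit for home events

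*Protocol article*

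**What the plan says.** The Safety evaluation section sets the expedited rule. Its trigger is worded "In the event of a severe adverse event (SAE", and the abbreviation list expands the term the same way: "SAE: Severe Adverse Event". Its time limit is that "the principal investigator and ethics committee should be fully informed within 24 h of the occurrence". Those two recipients are the ones "who are expected to provide guidance for further evaluation and management and make decisions on whether to suspend the trial".

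The same section has the type and severity of every adverse event entered on the CRF following each intervention. Sessions are weekly in both arms. Between sessions, the Tai Chi arm is told: "Participants will also be instructed to practice Tai Chi for 30 min daily at home". The control arm has the same daily 30 minutes of stretching.

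The Adherence section adds staff contact, in which participants are encouraged and "informed of the detailed exercise contents and benefits once a week via WeChat or telephone". It also requires participants to upload pictures or recordings of their home practice, and encourages a daily check-in on a WeChat mini-app. Table 1 lists adverse events at weeks 0, 6, 12 and 18, with no visit between weeks 12 and 18.

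Under Quality control there is an independent steering committee: "Steering committee consists of investigators with expertise in Tai Chi clinical trials, statistical design, exercise, and adverse events". Of its members the article says: "They are responsible for monitoring data, identifying problems, reviewing collected data, and controlling bias". The Safety evaluation section does not mention this committee.

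**The concern.** Two features of the rule do not do what an expedited rule is for.

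The first is the trigger. Severity describes how intense an event is; seriousness describes what it led to. Because the same section has severity recorded on the CRF, *severe* is naturally read as the top intensity grade. A fall leading to an overnight admission but graded moderate would then fall outside the rule, while an intense but harmless headache would fall inside it.

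The second is the clock. Staff cannot report what they have not heard of, so a limit counted from the event depends on how fast the participant reports. Most exercise is done unsupervised at home, the stated point of capture is the weekly session, and no session takes place after week 12.

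At stake is whether serious events in either arm reach the principal investigator and the ethics committee in time to inform the decision on suspending the trial. The primary outcome and its analysis are not affected.

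**Working it through.** The rule contains no derived figure to reproduce. The check sets the 24 h limit against the contact the article describes.

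**Share of exercise time away from staff, over 12 weeks**

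- Home practice, each arm (Interventions): 12 weeks × 7 days × 0.5 h = 42 h.
- Tai Chi classes: 12 × 1 h = 12 h. Home share: 42 / (42 + 12) = 42/54 = 78%.
- Control classes, counting only the 20 minutes of stretching in each: 12 × 20 min = 4 h. Home share: 42 / (42 + 4) = 42/46 = 91%.

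**Chance that a scheduled contact follows within 24 h**

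Assume an event is equally likely at any time. With contacts every *d* days, the share of events followed by a contact within one day is min(1, 1/*d*).

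| Contact counted | *d* (days) | Contact within 24 h | No contact within 24 h |
|---|---|---|---|
| Weekly session only | 7 | 1/7 = 14% | 86% |
| Weekly session and weekly call, evenly spaced (assumption) | 3.5 | 1/3.5 = 29% | 71% |
| Follow-up, week 18 visit only (6 × 7 = 42 days) | 42 | 1/42 = 2.4% | 98% |
| Daily check-in, always completed and used to report events (neither is stated) | 1 | 100% | 0% |

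The 7 and 42 days are the longest gaps between scheduled contacts. They are not expected reporting delays.

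**Trigger**

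No arithmetic applies. *Severe* appears in the rule and again in the abbreviation list. The article's only other use of the idea in this section is the severity entered on the CRF for every event. Nothing in the article ties the trigger to outcome, so the literal reading is intensity.

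**The case against.** The strongest reply is that the rule can be kept. Participants have WeChat and telephone links to the study, must upload evidence of home practice and are encouraged to check in daily. Nothing stops a participant or relative from reporting at once. The Discussion also mentions telephone questions and electronic CRFs during follow-up, without dates. This defeats any inference that the limit cannot be met or is breached by design. It does not remove the point: the uploads and check-ins are presented as feedback and encouragement for exercise, the check-in is optional, and an injured participant may simply stop using it.

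Second, *severe* may be loose English for *serious*, and the full protocol may hold a definition. The abbreviation list only expands the same term, so it is weak corroboration. That is fair, and a definition left to the full protocol is not a fault of the article. The point is the word that is stated: it is the wrong one if outcome is meant. Missed hospitalisations are a risk of the wording, not a demonstrated failure.

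Third, the figures have limits. The 78% and 91% are shares of exercise time, not of serious events, and no home practice is assigned after week 12, so they do not carry over to follow-up.

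A reader might also infer that the rule bypasses the steering committee. The article does not support that. The committee is unnamed in the rule, not excluded. It reviews collected data, and the CRF includes adverse events. Nor does the article say that suspension can follow only from this trigger.

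**Conclusion.** The point holds as a defect in a stated rule. Read literally, the trigger lets a serious event go unreported when it is not graded severe. The 24 h limit counted from the event is not assured by the stated contact schedule: scheduled staff contact alone would leave about 71% to 86% of evenly timed events without a contact in the window during the intervention, and about 98% in follow-up.

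Those shares assume uniform timing, evenly spaced calls and no report started by the participant. They fall to 0% if a daily channel is always used and carries event reports. The range is wide because the article does not say which channel carries them. The documents do not show that events will arrive late or never, and this conclusion does not claim it.

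The change is worth making, because recruitment has begun and the rule is in use.

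**What to change.** Four changes, the last optional:

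1. In Safety evaluation and in the abbreviation list, replace *severe* with *serious*, and define seriousness by outcome whatever the intensity: for example death, threat to life, hospitalisation or its prolongation, lasting disability, or another medically important event.
2. Count the 24 h from the time study staff become aware of the event.
3. Instruct participants in both arms to report any fall, injury or hospital visit promptly through the existing WeChat or telephone channel, up to week 18, and state that this channel is used for event reports.
4. Optionally, copy the report to the steering committee, to match its monitoring role under Quality control.

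Leave the suspension decision where the article puts it. Requiring the steering committee's view first would be a preference, and it could delay urgent action.

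The cost is protocol wording, one line in the participant instructions and, if wanted, one more recipient on an existing report. No visits or staff are added.
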